## Abstract

**Background:**

Universal Health Coverage ensures access to quality health services for all, with no financial hardship when accessing the needed services. Nevertheless, access to quality health services is marred by substantial resource shortages creating service delivery gaps in low-and middle-income countries, including Kenya. The Innovative Partnership for Universal Sustainable Healthcare (*i*-PUSH) program, developed by AMREF Health Africa and PharmAccess Foundation (PAF), aims to empower low-income women of reproductive age and their families through innovative digital tools. This study aims to evaluate the impact of *i*-PUSH on maternal and child health care utilization, women’s health including their knowledge, behavior, and uptake of respective services, as well as women’s empowerment and financial protection. It also aims to evaluate the impact of the LEAP training tool on empowering and enhancing community health volunteers’ health literacy and to evaluate the impact of the M-TIBA health wallet on savings for health and health insurance uptake.

**Methods:**

This is a study protocol for a cluster randomized controlled trial (RCT) study that uses a four-pronged approach—including year-long weekly financial and health diaries interviews, baseline and endline surveys, a qualitative study, and behavioral lab-in-the-field experiments—in Kakemega County, Kenya. In total, 240 households from 24 villages in Kakamega will be followed to capture their health, health knowledge, health-seeking behavior, health expenditures, and enrolment in health insurance over time. Half of the households live in villages randomly assigned to the treatment group where *i*-PUSH will be implemented after the baseline, while the other half of the households live in control village where *i*-PUSH will not be implemented until after the endline. The study protocol was reviewed and approved by the AMREF Ethical and Scientific Review Board. Research permits were obtained from the National Commission for Science, Technology and Innovation agency of Kenya.

**Discussion:**

People in low-and middle-income countries often suffer from high out-of-pocket healthcare expenditures, which, in turn, impede access to quality health services. Saving for healthcare as well as enrolment in health insurance can improve access to healthcare by building capacities at all levels—individuals, families, and communities. Notably, *i*-PUSH fosters savings for health care through the mobile-phone based “health wallet,” it enhances enrolment in subsidized health insurance through the mobile platform—M-TIBA—developed by PAF, and it seeks to improve health knowledge and behavior through community health volunteers (CHVs) who are trained using the LEAP tool—AMREF’s mHealth platform. The findings will inform stakeholders to formulate better strategies to ensure access to Universal Health Coverage in general, and for a highly vulnerable segment of the population in particular, including low-income mothers and their children.

**Trial registration:**

Registered with Protocol Registration and Results System (protocol ID: AfricanPHRC; trial ID: NCT04068571: AEARCTR-0006089; date: 29 August 2019) and The American Economic Association’s registry for randomized controlled trials (trial ID: AEARCTR-0006089; date: 26 June 2020).

## Background

There has been a renewed international commitment to Universal Health Coverage (UHC) aiming at ensuring all people have access to the health services they need without suffering from financial hardships. However, there are sustained resource shortages and service delivery gaps in many countries that prevent them from meeting the Sustainable Development Goal (SDG) 3.8 related to UHC (i.e., achieve UHC, including financial risk protection, access to quality essential health care services and access to safe, effective, quality, and affordable essential medicines and vaccines for all). Achieving UHC is particularly important in achieving SDGs related to maternal and child health (i.e., reducing the global maternal mortality ratio to less than 70 per 100 000 live births (SDG 3.1) and ending preventable deaths of newborns and children under 5 years of age (SDG 3.2). All countries are committed to reduce neonatal mortality to at least as low as 12 per 1000 live births and under-5 mortality to at least as low as 25 per 1000 live births by 2030. Evidence still shows that more than half of the world’s population lacks access to health care of sufficient quality [1] and about 100 million people fall into extreme poverty each year due to ill-health [2], particularly in low- and middle-income countries (LMICs). Systemic reforms are needed to translate commitment to UHC into a reality.

Despite being classified as a middle-income country in 2014, Kenya still remains among the 25% poorest countries strongly affected by social and health inequalities in the world. More than one third of Kenyans have an income below the poverty line (1.9 USD/day) [1–5]. Inequalities in access to healthcare, in particular maternal and child health care, are still rampant, despite major improvements made through targeted policies over the past few years [5]. For instance, according to the 2014 Kenya Demographic and Health Survey (KDHS), the maternal mortality ratio has marginally reduced to 362 per 100,000 live births, not statistically different from the figures reported in 2008–2009 [4]. While a substantial under-5 mortality reduction was achieved with a drop from 115 per 1000 live births in 2003 to 52 per 1000 live births in 2014, it is still twofold higher than the SDG target. These figures are disproportionately higher in Western Kenya, such as in Kakamega County. The poorest mothers are still far behind in terms of coverage of essential Reproductive and Maternal and Child Health services [4, 5].

However, there is little evidence on the effectiveness of intervention strategies in enhancing the coverage, integration, and implementation of maternal and child health services in primary healthcare system in developing countries, including Kenya. Interestingly, the Government of Kenya has included UHC as one of its “Big Four Agenda”-action points, which is anticipated to lead the transformation of the country by 2022 [3, 4]. The objective is to achieve a 100% cost subsidy for essential health services and to reduce out-of-pocket health expenditures by half. Low-cost health insurance schemes, eHealth, and mobile health (mHealth) services are among other opportunities to achieve this goal. Consequently, two non-governmental organizations, AMREF Health Africa and PharmAccess Foundation (PAF), are both supporting the Government to achieve the goal of UHC in many counties. This includes Kakamega—a county in Western Kenya—where AMREF and PAF are jointly implementing their Innovative Partnership for Universal Sustainable Healthcare (*i*-PUSH) program.

In order to maximize the effectiveness of this program, it is important for stakeholders to have a deep understanding of current access to health services, households’ health-related decision-making, and out-of-pocket health care expenditures in the target populations. The main aim of the study is to evaluate the impact of *i*-PUSH (most notably enhanced access to subsidized health insurance through the “health wallet” and increased community health volunteer (CHV) training opportunities through the LEAP training tool) on health care utilization, in particular related to maternal and child health, and financing of out-of-pocket health care expenditures. The evaluation research is conducted by two independent research institutes, namely, the African Population and Health Research Center (APHRC) and Amsterdam Institute for Global Health and Development (AIGHD). It is funded by the Dutch Postal Code Lottery, the Joep Lange Institute, and the Dutch Ministry of Foreign Affairs through the Health Insurance Fund.

## Methods/design

### Study site and period

*i*-PUSH has been ongoing in parts of Kakamega County since 2017. The study is being carried out in Khwisero Sub-county—one of the sub-counties in Kakamega County, where the *i*-PUSH program has expanded after the baseline survey. The implementing partners selected two health clinics that were considered to be included in the expansion of the *i*-PUSH program. Twenty-four (24) villages located in the catchment areas of these two clinics were randomly selected from a list of all eligible villages (*N* = 239) in the catchment areas. The list of villages was provided by the Sub-county government jointly with the *i*-PUSH program area manager. Random selection was done by the research team using a computer program to generate a short list of villages from the longlist, to be randomly assigned to either the treatment or the control group. Villages cover on average about 100 households. Each village is served by one unique CHV.

### Study design and randomization procedure

The survey design is a longitudinal cluster randomized controlled trial (RCT). Randomization occurs at the level of villages in Khwisero Sub-county in Kenya. The “treatment” and “control” groups are constructed, comparing villages where *i*-PUSH has been rolled out after the baseline with villages where *i*-PUSH would not roll out until after the endline. The research team used community-level socio-demographic and infrastructure indicators (including number of households, village-level access to basic amenities and public services, adult literacy rate, women literacy rate, perceived health status, and healthcare utilization indicators) from baseline data to form pairs of similar villages and determine the exact matching indicators.

In keeping with robustness of the cluster RCT, the procedure hence followed four steps for matching of the “treatment” and “control” villages: (i) purposive selection of the Sub-county (Khwisero) where the intervention rolled out, (ii) random selection of 24 villages, (iii) pair-matching of villages based on relevant background characteristics and baseline outcomes of interest, and (iv) randomization of treatment and control villages within each pair of villages by flipping a coin. Pairing villages before randomization reduces the risk of a bad draw during the randomization process. Randomization without pairing would, in expectation, also lead to similar control and treatment groups, but it was also possible that the random draw produces a control and treatment group with very different characteristics by chance [6]. This risk was reduced through pairing. We used the Euclidean distance for our matching process, which corresponds to the absolute difference between the standardized values of all of the covariates for a possible pair of matches. We conducted the matching within each of the four originally selected health clinic catchment areas separately. Thus, each village was matched with one of the other five villages in the vicinity of the health clinic. This was done to ensure that each health clinic had an equal number of treatment and control villages in their catchment area. Hence, we computed this distance measure between each village and all other villages within the same health clinic catchment area; “pair” the two villages with the minimum distance and remove them from the list; repeat the distance calculation excluding the pair made; and continue until all villages were paired.

After the matching process, the randomization assignment was carried out in the presence of key stakeholders including PAF, local liaison persons and village representatives, upon explaining all steps. Consent for the procedures was obtained from local government officials before the random assignment. The following steps were followed: papers with paired village names were folded and put in a bag; and two village representatives from each paired village discussed on whom to pick the paper and after the other group members verified that the names could not be seen, one paper was picked. A Kenya Shilling 10 coin was used to decide which group the picked village belonged to by flipping the coin. The village representatives had decided that the head of the coin should represent the control group, justifying that Kenyatta (1st president of Kenya) was a “controlling village” and the shield to represent the intervention group. The process of choosing the folded paper and flipping of the coin was repeated for all paired villages.

The treatment group thus consists of the target population living in the randomly assigned 12 treatment villages. *i*-PUSH roll out in the treatment villages includes training of their CHVs with the LEAP tool, who subsequently introduced the health wallet to eligible women living in the treatment villages they serve, and offer them the subsidized insurance scheme on their mobile phone. The CHVs working in the control villages (as well as the remaining non-sampled villages on the longlist) have not received training on the LEAP tool until endline, nor were women in the control villages offered the health wallet and subsidized insurance on their mobile phone.

We randomized at the village level because (1) villages are served by one CHV each, who are either trained or not trained on LEAP (hence, the LEAP intervention cannot be varied within villages); (2) to avoid contamination between households within the same villages regarding health-related knowledge and behavior; and, (3) moreover, it was deemed politically unfeasible to offer the health wallet and subsidized health insurance to some eligible households in a village but not to other eligible households in that same village. Upon roll out of the subsidized health services, eligible households were encouraged to use the services, though they were given the right to opt out at any time.

### Study population

The study population consists of eligible households living in the selected study villages. Eligible households included those with at least one woman of reproductive age (WRA) (18–49) who (a) had at least one child below 4 years living with her at baseline or (b) was pregnant at baseline. Data on all household members are also collected from these eligible households.

Selected CHVs and PAF’s area manager provided the full list of households and other necessary information within the work area of each CHV. Based on the household demographics and pregnancy information, eligible households were identified. Initially, the study sought a 50-50 allocation between households with a pregnant woman and households with a child under 4 years old. After the household listing exercise, it became clear that there were too few pregnant women in each village to fulfill this criterion. We then decided to include all pregnant women in our sample and randomly sample additional households with children under 4 years old until the cluster size (10 households per village) was achieved. The research team did a random selection as follows: all eligible households with children under 4 years old were entered in a spreadsheet and receive a randomly assigned number. The team ordered the households per CHV based on this random number, and the first 10 households per CHV in each village were included in the study sample. Additional eligible households per CHV were over-sampled to serve as replacement households for dropouts.

### Sample size

Sample size calculation followed Hemming et al. [7]’s study by fixing the number of clusters per arm to be 12 clusters, and then estimated the cluster size and total sample size. In the current study, it was assumed that the *i*-PUSH program could yield an effect size of 0.4 standard deviation in terms of health care utilization with an intracluster correlation (ICC) of *ρ* = 0.014. The estimates of the ICC were derived from Geng et al. [8]’s, study conducted in Nandi County which used high-frequency data on diaries on health-seeking behaviors and financial expenditures over 1 year (October 2012–October 2013). The calculation of the ICC was based on health care utilization measured as visits to any formal health provider, unconditional on reported health symptoms. It hypothesized a confidence interval of 95%, a margin-of-error of 5%, and a power of 80%. With a cluster size per arm of 12 clusters, and a total number of women per cluster of 10, the total sample size was 120 households per arm and 240 households for the full study.

To keep sample size at par, households that dropped out of the study before the start of the intervention were replaced with new eligible households on a rolling basis for a maximum period of six months, or until the program started.

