Quantitative data will be analyzed using Stata version 14 statistical software. The first set of analysis will consist of descriptive statistics and will summarize and compare using measures of central tendency and dispersion (mean (SD), range and median). This will allow us to examine participants’ characteristics across the different sub-groups. We will first check whether the outcomes and covariates in the control group and treatment group are comparable at baseline using *t* test adjusted for clustering at the village unit for continuous variables and cluster-adjusted chi-square for binary variables. The second set of analysis will consist of assessing the causal effect of the *i*-PUSH intervention via an analysis of covariance (ANCOVA) based on intention-to-treat (ITT) analysis (all respondents who are randomized will be included in the statistical analysis and will be analyzed according to the group they were initially/originally assigned). To account for clustering of data at the village level, multi-level mixed models will be used. In addition, a generalized linear mixed model for repeated measures with random components will be used.

Based on our research questions, we will explore several additional econometric models. We will explore the impact of the *i*-PUSH program on health outcomes (healthcare utilization, health status, percentage of children who are fully immunized, etc.) and financial outcomes (percentage of women using NHIF/MTIBA to access services, percentage of people enrolled in NHIF through M-TIBA, percentage of people saving through M-TIBA, total amount saved on M-TIBA, etc.) via an analysis of covariance (ANCOVA) based on ITT analysis. Since we will have several rounds of data collection on the same respondents, we will combine all rounds of data collection (baseline and follow-up waves), and we will run an ANCOVA econometric model on a pooled panel data. More specifically, in the econometric model below, we will regress the follow-up measurement of the outcome variable (dependent variable) on the following covariates: baseline measurement (pretest measurement) and treatment group while controlling for the baseline socio-demographic characteristics such as maternal age, education, socioeconomic status (wealth quintile), crowding (persons per room), occupation, etc. The considered model is thus:
1$$ {Y}_{ij}={\alpha}_0+{\alpha}_1{X}_{ij0}+{\alpha}_2{\mathrm{Treament}}_{ij}+{e}_{ij t}, $$

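### Replacement of dropouts is tied to programme start rather than to the public coin flip, so as written households may leave or be enrolled after their village's allocation is known

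*Protocol article*

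**What the plan says.** Under Sample size, to hold the numbers at the planned level, "households that dropped out of the study before the start of the intervention were replaced with new eligible households on a rolling basis", and this continues "for a maximum period of six months, or until the program started". The limit is a duration or the start of the programme. Randomisation is not mentioned.

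Under Study design and randomization procedure, village indicators were taken "from baseline data to form pairs of similar villages". The last of the four steps was "randomization of treatment and control villages within each pair of villages by flipping a coin". The draw was open: "the randomization assignment was carried out in the presence of key stakeholders including PAF, local liaison persons and village representatives". Roll-out followed the draw: "The treatment group thus consists of the target population living in the randomly assigned 12 treatment villages".

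Under Study population, extra eligible households were sampled for each community health volunteer as a reserve to replace dropouts.

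Under Data management and analysis, the intention-to-treat (ITT) rule is that "all respondents who are randomized will be included in the statistical analysis and will be analyzed according to the group they were initially/originally assigned".

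**The concern.** In a cluster trial, random allocation of villages protects the comparison only if the households followed were fixed before allocation was known, or if later changes are unrelated to it. Here the original households were surveyed before the flip, which is sound. The replacement rule then leaves the sample open for a further interval in which allocation may be known locally.

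Two things could then differ by arm: who leaves and who agrees to step in. Control households, for example, face continued weekly interviews with no programme until after endline. Matching villages beforehand cannot correct a change in household composition that comes after the flip.

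Three features of the plan raise the stakes:

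- The primary outcome is a count of visits over the whole baseline-to-endline period, so leavers and late substitutes contribute shorter observation.
- The main model adjusts for a pretest value. For a post-flip substitute, that value is measured after allocation.
- The ITT rule speaks of randomised respondents, but the article does not say how it treats a household that leaves between flip and roll-out, or the household that takes its place.

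**Working it through.** **Order of events.** Pairs were built from baseline data, so baseline precedes pairing. Pairing is the third step and the coin flip the fourth. The programme goes only to villages that the flip assigned to treatment, so roll-out follows the flip. The order is baseline, pairing, flip, programme start. Replacement may run to programme start, subject to the six-month limit, so the stated window can include the time between flip and start. No other section closes it earlier.

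**Length of the gap.** The article dates neither the flip nor programme start, and the Table 1 schedule is not available. Its durations point in different directions:

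- Expected outcomes gives 18 months of follow-up, and endline is about 12 months after introduction. If the 18 months run from baseline, baseline to start is 18 - 12 = 6 months.
- The abstract calls the diaries year-long, and they span baseline to endline. On that reading the gap is 12 - 12 = about 0 months.

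The flip lies somewhere inside an interval of roughly 0 to 6 months.

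**The plan's own sample size.** Inputs from Sample size: effect 0.4 SD, ICC 0.014, 12 clusters per arm, 80% power, 5% level (read as two-sided).

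- Individually randomised: n = 2 × ((1.960 + 0.842)/0.4)² = 98.1 per arm.
- Cluster size with k = 12: m = n(1 - ρ)/(k - nρ) = 98.1 × 0.986/(12 - 98.1 × 0.014) = 9.1, rounded up to 10.
- Total: 12 × 10 = 120 per arm, 240 overall. The stated figure reproduces.
- Design effect at m = 10: 1 + 9 × 0.014 = 1.126. Normal-approximation power is 83.1% (79.7% using t on 22 df).
- Standard error of the contrast: √(2 × 1.126/120) = 0.137 SD.

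**Illustrative shift.** The article gives no replacement rate and no difference between leavers and substitutes. Both are assumed: a share r of one arm is swapped after the flip, and the incoming households differ from those they replace by d SD. Then shift = r × d, and two-sided type I error = 1 - Φ(1.96 - shift/0.137) + Φ(-1.96 - shift/0.137).

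| r (households of 120) | d (SD) | shift (SD) | share of 0.4 SD | type I error |
|---|---|---|---|---|
| 5% (6) | 0.2 | 0.010 | 2.5% | 5.1% |
| 5% (6) | 0.5 | 0.025 | 6.3% | 5.4% |
| 10% (12) | 0.2 | 0.020 | 5.0% | 5.2% |
| 10% (12) | 0.5 | 0.050 | 12.5% | 6.5% |
| 20% (24) | 0.2 | 0.040 | 10.0% | 6.0% |
| 20% (24) | 0.5 | 0.100 | 25.0% | 11.3% |

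The table ignores baseline adjustment, which would absorb part of any shift.

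**Cost of leaving replacements out.** If both arms fall by 5%, 10% or 20% with no replacement, normal-approximation power falls from 83.1% to 81.5%, 79.6% or 75.3%.

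**The case against.** The strongest reply is that nothing shows any post-flip replacement took place. Every dropout may have been replaced before the draw, and the six-month limit may have run out first. This stands. The defect lies in the rule as written, and a reader who infers that the sample was in fact compromised goes beyond the text.

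Second, substitutes were not openly recruited. They came from a reserve sampled for the purpose, described directly after the random ordering of eligible households. This stands in part. It narrows staff discretion, but the article does not say the reserve was used in random order, and a reserve does not stop households leaving or declining in the light of their allocation.

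Third, a reader might infer that free insurance drew households into the study in treatment villages. The text does not support that. The offer went to eligible women living in the treatment villages, and restricting it to some eligible households was judged politically unfeasible. Cover depended on residence and eligibility, so there was little reason to join the diaries to obtain it. Differential dropout is the more plausible route. Even household knowledge of allocation is an inference, since the draw is described as attended by stakeholders and village representatives.

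Fourth, a reader might call the replacement rule a contradiction of ITT. Villages are the randomised units, so a substitute from the same village is still analysed in its assigned cluster, and the article nowhere says a leaver's data are discarded. The conflict is potential. What remains is that the ITT rule and the replacement rule are not reconciled for leavers and substitutes after the flip.

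**Conclusion.** The concern holds in a limited form. The article's own sequence places the public flip before programme start, and its replacement rule runs to programme start, so exit and entry after allocation is known are permitted and nothing in the text rules them out. The number of such replacements, their split by arm and the length of the interval cannot be recovered from the article.

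The size is therefore conditional. Under the assumed ranges (5-20% of one arm, 0.2-0.5 SD difference) the shift is 0.01-0.10 SD, or 2.5-25% of the planned effect, with type I error of 5.1-11.3%. The range shows that the effect could run from negligible to material. It is not an estimate for this trial. If replacement in fact ended before the flip, the concern is settled by one sentence saying so.

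**What to change.** 1. Anchor the ITT set to the households enrolled on the date of their pair's coin flip.
2. State that replacement stops at the flip. If it did not, record for each replacement whether it was enrolled before or after the flip.
3. Analyse the primary outcome with and without post-flip replacements.
4. Report dropouts and replacements by arm and by before/after the flip.
5. Keep households that left after the flip in the ITT set, and handle their incomplete follow-up with an exposure offset (a visit rate) or a missing-data method. Their truncated visit counts should not enter as raw totals beside full-period totals. That would mix unequal observation times and, if dropout differs by arm, add a bias of its own.

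The cost is analysis-set wording, one date flag and one further analysis. The analysis without post-flip replacements loses some precision. The loss is small if they are few: a 5% loss in both arms takes planned power from 83.1% to 81.5%. At 20% it falls to 75.3%, which is a further reason to report the actual number.
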